Despite the observed effects of household air pollution on cardiometabolic disease indicators from our formative study, residual confounding and lack of temporality are major limitations to cross-sectional designs, calling for the need for a randomized study with repeated measures of exposure and health outcomes. Although evidence suggests improvements in health following reductions in ambient air pollution exposures, much less is known about whether or not efforts to reduce exposures to emissions from household solid fuel combustion will result in health benefits, and if certain subgroups of the population are more likely to see improvements [29]. Furthermore, a better understanding is also needed on the barriers surrounding cookstove adoption and sustained use [18]. We propose that sustained use of a carefully selected, culturally appropriate, wood-burning cookstove with an engineered combustion chamber and chimney (the *Justa* cookstove) will result in lower air pollution exposures and better health status compared to the use of the traditional cookstove. Within a community-engaged framework among rural Honduran women, this cookstove intervention addresses the following aims through an individual-level, stepped-wedge randomized controlled trial:

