### Aim 1: in an intent-to-treat framework, evaluate the impact of the *Justa* cookstove intervention on indicators of cardiometabolic disease risk

Among 230 female primary cooks, we will evaluate 3 primary health endpoints (blood pressure, C-reactive protein [CRP], and HbA1c) among those randomly assigned to using traditional and *Justa* cookstoves during a 3-year project with 6 study visits, spaced approximately 6 months apart. Secondary health endpoints include indicators of other cardiometabolic- and respiratory-related outcomes, specifically metabolomics and other biomarkers of systemic injury and inflammation from dried blood spots, augmentation index, central pulse pressure, blood lipids, self-reported health symptoms, fractional exhaled nitric oxide, and telomere length from buccal cells. We will evaluate the potential for effect modification by age, blood pressure, diabetes, body mass index (BMI), waist circumference, and metabolic syndrome. *We hypothesize that use of the Justa cookstove (intervention) will result in improved indicators of non-communicable disease risk as compared to use of the traditional cookstove among Honduran women.*

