Metabolic syndrome, a cluster of cardiometabolic conditions that occur together, will be defined by current international guidelines and modified for non-fasting lipids: waist circumference ≥ 80 cm plus any 2 of the following, triglycerides > 200 mg/dL, high-density lipoprotein < 50 mg/dL, systolic blood pressure ≥ 130 mmHg, diastolic blood pressure ≥ 85 mmHg, and HbA1c > 5.6% [24, 40, 41].

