### Statistical analysis

We will conduct a descriptive analysis of the exposures, health endpoints, and other measured characteristics (Table 2). Quantitative summaries will include means, standard deviations, ranges, and frequencies as appropriate for the data type. Descriptive statistics will be utilized to assess the similarity of participant characteristics across study arms.

Primary analyses will evaluate the association between assigned cookstove type and the 3 primary health endpoints (blood pressure, CRP, HbA1c) in an intent-to-treat framework. We will use a linear mixed model with a fixed effect for assigned cookstove type (traditional or *Justa*), the independent exposure variable of interest. The model will include a random effect for each participant to account for correlation from repeated measures within person. To account for potential changes in the outcomes over time the model will include visit date using a spline trend function. Letting *Y*_*ij*_ denote the health endpoint measurement for participant *i* at visit *j*, *x*_*ij*_ denote the assigned cookstove type (0 for traditional, 1 for *Justa*) for participant *i* at visit *j*, and *t*_*ij*_ denote the time of visit *j* for participant *i*, this model can be written:1$$ {Y}_{ij}=\mu +{a}_i+\beta {x}_{ij}+f\left({t}_{ij}\right)+{\epsilon}_{ij}. $$

In Eq. (1), *β* represents the intervention effect on the outcome measure and is the primary quantity of interest. The parameter *μ* represents the overall average outcome value, *a*_*i*_ represents the random effect for participant *i*, and *ϵ*_*ij*_ is an independent error term. We will use natural cubic splines as the function of time *f* in the model, with the complexity of the adjustment controlled by the number of spline functions.

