For the exposure-response analysis, we will use a linear mixed model similar to the model used in the intent-to-treat analysis. In this framework, the personal and kitchen PM_2.5_ measurements will be included as the exposure variable *x*_*ij*_ in Eq. (1). As the exposure-response approach will not utilize the study’s randomization to control for confounding, potential confounders identified a priori will be included in Eq. (1) as additional fixed effect terms. Potential confounders include participant age, indicators of socioeconomic status (e.g., household possessions, participant education level, beds per person in each household), physical activity levels, BMI, and dietary intake. We will also conduct a “per protocol” analysis using self-reported actual cookstove use, rather than assigned cookstove.

We will evaluate effect modification by adding the following variables as interaction terms with the stove assignment or exposure measurement variable in separate models: age (< 40 or ≥ 40 years), blood pressure (normal systolic < 120 and diastolic < 80 vs. borderline high/high systolic ≥ 120 or diastolic ≥ 80), diabetes status (normal hbA1c < 5.7% vs. pre-diabetic/diabetic ≥ 5.7%), BMI (normal < 25 or overweight/obese ≥ 25), waist circumference (< 80 cm vs. ≥80 cm), and metabolic syndrome (presence vs. absence).

Sensitivity analyses will be conducted to assess the impact of different forms of the adjustment for time in Eq. (1) by varying the number of spline functions and considering alternative representations such as indicators of season or visit number. We will also conduct sensitivity analyses that exclude women who were taking medications that could influence inflammation in the body, such as hypertension or vitamins, or who were ill at the time of the health measurements. Additional sensitivity analyses will exclude air pollution samples that came from pumps that ran for less than 24 h, and flow rates that strayed outside the 10% pre- and post-sampling range.

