The sample size of 230 was selected based on feasibility and cost considerations and is well-powered for the primary analyses. We estimated power by conducting a simulation that generates data according to the study design and Eq. (1). For the blood pressure model: assuming a standard deviation of 12 mmHg for systolic blood pressure [26], a correlation of 0.76 between repeated measures from the same individual [47], and a 10% loss to follow-up, we estimate there will be 80% power to detect a difference of 1.81 mmHg. This difference is smaller than that observed in the only cookstove randomized controlled trial conducted among non-pregnant women in Guatemala [7]. The power remained constant adding linear trends of 3 mmHg/year and seasonal trends of amplitude 3 mmHg to the simulated blood pressure measurements. For the CRP model: assuming a standard deviation of 1.1 mg/dL [48], a correlation of 0.66 [49] between repeated measures from the same individual, and a 10% loss to follow-up, we estimate there will be 80% power to detect a difference of 0.2 mg/dL. Although different cooking fuels and sources of indoor pollution were investigated, this difference in CRP is similar to that observed in a random crossover design evaluating the impact of indoor air filtration among homemakers in Taiwan [50].

For missing data, we will record the number, timing, pattern, and reason. Missing data may occur due to subject-initiated drop out, missing visits, instrument failure, and data entry error. We will evaluate whether the missing data patterns are differential between study arms, or by study visit. For all analyses, we will assume missing data to be missing at random a priori.

Data will be analyzed using SAS® software version 9.4 (SAS Institute, Inc., Cary, NC, USA) and R Statistical Software (The R Project for Statistical Computing).

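### Blood pressure, HbA1c and metabolic syndrome status are effect modifiers in models whose outcome is blood pressure or HbA1c, and neither plausible way of classifying women gives a valid subgroup result

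*Protocol article*

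**What the plan says.** The primary analysis in the Statistical analysis section concerns "the association between assigned cookstove type and the 3 primary health endpoints (blood pressure, CRP, HbA1c) in an intent-to-treat framework". Eq. (1) has a random intercept per woman and one spline of visit date shared by all women.

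The same section then adds modifier-by-stove and modifier-by-PM2.5 terms, one modifier at a time: "We will evaluate effect modification by adding the following variables as interaction terms with the stove assignment or exposure measurement variable in separate models". Two of the modifiers are "blood pressure (normal systolic < 120 and diastolic < 80 vs. borderline high/high systolic" (120 mmHg or above, or diastolic 80 or above) and "diabetes status (normal hbA1c < 5.7% vs. pre-diabetic/diabetic" (5.7% or above). A third is metabolic syndrome, which the Health endpoints section defines as "waist circumference ≥ 80 cm plus any 2 of the following"; the list that follows includes systolic pressure, diastolic pressure and HbA1c.

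Aim 1 states the general intention: "We will evaluate the potential for effect modification by age, blood pressure, diabetes, body mass index (BMI), waist circumference, and metabolic syndrome". Aim 2 repeats it for PM2.5. No section exempts a modifier that is also the outcome. Table 2 shows blood pressure and HbA1c measured at all six visits, and no section says which visit sets a woman's status.

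**The concern.** When the outcome defines the subgroup, part of what puts a woman in the 'high' group is a chance high reading. Table 1 has every woman on a traditional stove at visits 1 and 2. A chance high at a baseline visit is therefore always a control observation, and her later return to her usual level falls largely in *Justa* time. With one time curve for everybody, the model can place that return only in the stove-by-status term. This needs no stove effect, no trend and no flaw in randomisation.

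Re-classifying at each visit creates a different problem, because the model then conditions on its own outcome.

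The Background gives as a gap in knowledge "if certain subgroups of the population are more likely to see improvements". The subgroup results are meant to inform that question, and in these models they could not do so.

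**Working it through.** **Inputs from the protocol article.** SD 12 mmHg and "a correlation of 0.76 between repeated measures from the same individual"; 230 women, 115 per arm; 10% loss; *Justa* after visit 2 (arm 1) or visit 4 (arm 2); six visits. **Assumed, because not given:** two-sided 5% level, mean systolic pressure of 112-128 mmHg, visit dates at the middle of the Table 1 windows, and loss treated as 206 completers.

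**1. The plan's own figure.** Detectable difference = (1.96 + 0.84) x SE of beta under Eq. (1). With 206 completers and 3, 4 or 5 spline functions this gives 1.80, 1.83 and 1.84 mmHg. With 230 women and gradual 10% dropout it gives 1.76-1.80. The stated 1.81 mmHg reproduces, so the set-up matches the plan's.

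**2. The false interaction by hand** (cut at the mean, no stove effect).
- Gap between 'high' and 'normal' women at the classifying visit: 2 x 0.798 x 12 = 19.1 mmHg.
- Gap at every later visit: 0.76 x 19.1 = 14.6 mmHg. The fall is 4.6 mmHg.
- Stove indicator at visit 1, centred within woman: 0 - 4/6 = -2/3 in arm 1; 0 - 2/6 = -1/3 in arm 2.
- Its within-woman sum of squares: 2 x (2/3)^2 + 4 x (1/3)^2 = 4/3 in arm 1; 4 x (1/3)^2 + 2 x (2/3)^2 = 4/3 in arm 2.
- Within-woman estimate of the interaction: 4.6 x (-2/3 - 1/3) / (4/3 + 4/3) = -4.6 / 2.67 = **-1.72 mmHg**.

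Both arms contribute in the same direction, so randomisation does not cancel the bias. The shared time term cannot absorb it, because the two strata move in opposite directions.

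**3. Simulation of the interaction model** (random intercept, estimated variance components, no stove effect, status from visit-1 systolic pressure at 120).
- False interaction about -1.7 to -1.8 mmHg over means 112-128; the interaction test rejects in about 56-70% of trials.
- At mean 120, one run gives an apparent effect of -0.86 in 'high' and +0.81 in 'normal' women.
- Considered alone, the false benefit in 'high' women is significant in about 12-30% of trials and the false harm in 'normal' women in about 9-33%. Both together occur in at most 0.4%.
- With a uniform true effect of -1.81: about -2.67 in 'high' and -1.00 in 'normal' women.
- Other pre-stove rules behave alike: mean of visits 1-2, -1.79 (71% rejection); last pre-stove visit, -1.63 to -1.70 (59-63%); the full systolic-or-diastolic rule at visit 1, -1.64 to -1.67 (58-65%). For a diastolic outcome, -1.03 to -1.07 (44-47%). The rules that use diastolic pressure need its mean, SD and correlation with systolic, all assumed.
- Replacing the spline by visit indicators, one of the planned sensitivity analyses, leaves it at -1.66 (66%).

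**4. Status re-classified at each visit** (mean 120). With no stove effect the interaction is 0.01 and rejection 4.3%. A true -1.81 is estimated at about -1.0 to -1.1 in both strata.

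**5. HbA1c and PM2.5 interactions** (pre-stove status, inputs assumed throughout). HbA1c with SD 0.4-0.5, correlation 0.6-0.9 and mean 5.4-5.6%: false interaction -0.02 to -0.10 percentage points, rejection 29-87%. Systolic pressure on log kitchen PM2.5, with log SD 0.8 and 61% lower PM2.5 on the *Justa*: +0.64 to +0.65 mmHg per log unit, rejection 24-29%.

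**6. Remedies** (mean 120, no stove effect, status from visit 1).
- Fit visits 2-6: interaction +0.05, rejection 4.1%; SD of the estimate rises from 0.69 to 0.80.
- Keep all visits, with visit indicators by stratum: +0.03, rejection 5.0%; SD 1.40. A four-function spline by stratum leaves +0.32 and 6.1%.
- If the correlation instead falls 5% per extra visit (assumed), fitting visits 2-6 still leaves about -1.7 mmHg and 48-49% rejection. Stratum-specific time keeps rejection at about 5-7%.

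**The case against.** The strongest reply is that the article never says status is taken before the stove, never writes an equation for the interaction models, and gives one generic list of modifiers for all outcomes. The classifying visit is a detail that an analysis plan may settle. This stands in part: regression to the mean is a consequence of one reading and not a stated feature of the plan. It does not dispose of the point. The article fixes the cut-points, the interaction structure and the outcomes without exempting the overlap, and the other natural reading also gives a wrong answer.

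A reader might infer that the trial would usually report a benefit in hypertensive or prediabetic women and a harm in the rest. The figures do not support that. It is the interaction test that rejects in most null trials. Each subgroup-specific claim reaches significance in only about 10-30%, and both together almost never. For prediabetic women the documents give no HbA1c SD or correlation, so no size can be taken from them.

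It is also fair to say that these are secondary analyses. The primary beta, the 1.81 mmHg figure and the age modifier are unaffected. BMI and waist circumference do not contain the outcome, and CRP models are touched only through any correlation between CRP and the modifier.

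**Conclusion.** The concern holds in a limited form. Where blood pressure, diabetes or metabolic syndrome status modifies an outcome that it contains, the planned model gives either a false interaction or an attenuated effect, depending on an unstated choice. Under pre-stove classification with that reading kept as an outcome and a common time function, the false systolic interaction is about as large as the main effect for which the trial is powered. That size rests on the plan's SD and constant correlation, and on an assumed mean and significance level. Sizes for HbA1c, diastolic pressure and PM2.5 rest on assumed inputs and are indicative only. The point should be fixed before the effect-modification results are reported. It does not threaten the primary analysis.

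**What to change.** State that every effect modifier is fixed at its visit-1 value. Where the modifier contains the outcome (blood pressure status for systolic or diastolic pressure, diabetes status for HbA1c, metabolic syndrome for both), leave visit 1 out of the outcome data and fit visits 2-6, in the stove models and the PM2.5 models alike.

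Add a sensitivity analysis for these models in which time differs by stratum, preferably as visit indicators. It is needed because leaving out visit 1 removes the bias only if the within-woman correlation is constant over time, as Eq. (1) assumes.

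The cost is wording, with no new data. The interaction standard error grows by about 15-20% in the affected models (0.69 to 0.80 in the run above) and about doubles in the stratum-specific-time check (0.69 to 1.40), so that check will have low power.

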### Trial design

We utilized an individual-level, stepped-wedge randomized controlled trial design, with 230 women using traditional wood-burning cookstoves at baseline. Women were randomly assigned into study arms 1 and 2 by blindly drawing a number from a bag at a community meeting. Six repeated measures occurred over the 3-year study period from August 2015 through May 2018 (Table 1). Study arm 1 (*n* = 115) received the *Justa* cookstove intervention after visit 2, and arm 2 (*n* = 115) received the intervention after visit 4 (Table 1). A unique benefit of the stepped-wedge design is that each study arm provides before and after observations, and each arm switches from ‘control’ status to ‘intervention’ status over the course of the study, but not at the same time [31].

**Table 1 Tab1:** Study scheme for timing and visits of interventions, Honduras, August 2015 – May 2018

Stepped-wedge randomized controlled trial		
Timing of study visits for data collection	Arm 1 (*n*=115) Stove type	Arm 2 (*n*=115) Stove Type
Visit 1: Aug – Dec 2015	Traditional	Traditional
Visit 2: Jan – May 2016	Traditional	Traditional
	Arm 1 receives intervention	
Visit 3: Sep – Dec 2016	*Justa*	Traditional
Visit 4: Feb – May 2017	*Justa*	Traditional
		Arm 2 receives intervention
Visit 5: Sep – Dec 2017	*Justa*	*Justa*
Visit 6: Feb – May 2018	*Justa*	*Justa*

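### Season indicators, listed as an alternative to the time spline, would on the plain reading leave a calendar trend unadjusted in that sensitivity analysis

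*Protocol article*

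**What the plan says.** Eq. (1) in the protocol article (Statistical analysis) has a participant random intercept, a fixed effect for assigned stove and one function of time, f(t). The reason given for that function is: "To account for potential changes in the outcomes over time the model will include visit date using a spline trend function". It is a natural cubic spline and the only term that handles change over time.

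The sensitivity paragraph of the same section then varies the form of this adjustment, first by changing the number of spline functions and then by "considering alternative representations such as indicators of season or visit number". Season is not defined, and nothing says whether a trend term stays in the model beside it.

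Table 1 (Trial design) puts visits 1, 3 and 5 in August or September to December, and visits 2, 4 and 6 in January or February to May. Arm 1 has the Justa stove from visit 3 and arm 2 from visit 5.

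The power paragraph includes a drift scenario: "The power remained constant adding linear trends of 3 mmHg/year and seasonal trends of amplitude 3 mmHg to the simulated blood pressure measurements".

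**The concern.** In a stepped-wedge trial the share of participants on the intervention rises with calendar time, so any common drift in the outcome is confounded with the intervention unless the model removes it. Here the share assigned to Justa is 0, 0.5 and 1 across the three years, and it follows this same pattern in both visit seasons. Recurring season indicators are therefore balanced against stove and carry no information about drift. If they take the place of f(t), the stove coefficient is an unadjusted before-after contrast.

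The run is meant to show whether the result is robust to the choice of time adjustment. With drift present it could contradict a sound primary result. It could also appear to confirm a benefit that is only a downward drift. Because it is the most precise of the candidate models, it could be given more weight than it deserves. The same model form would be used for CRP and HbA1c.

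**Working it through.** **Inputs** (protocol article, Statistical analysis and Table 1): "assuming a standard deviation of 12 mmHg for systolic blood pressure"; "a correlation of 0.76 between repeated measures from the same individual"; 115 women per arm; 10% loss, taken as 115 × 0.9 = 103.5 per arm with complete data. Assumed: two-sided alpha of 0.05 (not stated) and visits at the middle of the Table 1 windows, i.e. 0, 5, 12.5, 17.5, 24.5 and 29.5 months.

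**Variance components.** Between-person variance is 0.76 × 144 = 109.44 and residual variance 34.56. With six visits the shrinkage factor is 6 × 109.44 / (34.56 + 6 × 109.44) = 0.95. Stove sequences are (0,0,1,1,1,1) and (0,0,0,0,1,1). All terms below are per woman per arm, in units of 1/34.56.

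1. *No time term.* Stove: (4 − 0.95 × 16/6) + (2 − 0.95 × 4/6) = 1.467 + 1.367 = 2.833. Removing the intercept: 2.833 − 0.3²/0.6 = 2.683. SE = √(34.56 / (103.5 × 2.683)) = 0.353.

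2. *Reproducing the stated power with a linear time term.* Centre time at its mean of 14.83 months. The stove-by-time cross-product is 24.67 + 24.33 = 49.0, and the sum of squares of time over both sequences is 2 × 637.8 = 1275.7. The information becomes 2.683 − 49.0²/1275.7 = 0.801, so SE = √(34.56 / (103.5 × 0.801)) = 0.646. The detectable difference at 80% power is (1.96 + 0.84) × 0.646 = 1.81 mmHg, which is the protocol's figure. The power claim therefore belongs to a model that adjusts for trend.

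3. *Season only.* Code season as −½ and +½. Its cross-product with stove is zero in each arm: visits 3 to 6 contribute −, +, −, + in arm 1, and visits 5 and 6 contribute −, + in arm 2. The stove estimate and its SE therefore equal those of step 1, where there is no time term. Bias per unit of linear trend = 49.0 / 2.683 = 18.3 months = 1.52 years.

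4. *Result when the true stove effect is zero.* Approximate rejection is Φ(bias/0.353 − 1.96).

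| Common trend, mmHg/year | Season-only bias, mmHg | False positives |
|---|---|---|
| 0.5 | 0.76 | 58% |
| 1 | 1.52 | 99% |
| 3 | 4.57 | essentially 100% |

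5. *Models that keep a trend.* With visit-number indicators, only visits 3 and 4 separate the arms: SE = √(34.56 / (103.5/2 × 1.367)) = 0.699, a detectable difference of 1.96 mmHg and zero bias. Season plus a linear trend also gives zero bias, SE 0.699 and 1.96 mmHg.

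6. *Check by simulation* (REML random-intercept fits, visit dates uniform within windows, 10% monotone dropout, 300-400 runs). Season-only gave 0.70 mmHg with 50% rejection at 0.5 mmHg/year, 1.51 mmHg with 99.8% at 1 mmHg/year, and about 4.5 mmHg with 100% at 3 mmHg/year. At 3 mmHg/year, season plus linear trend, season plus spline and visit-number indicators all gave bias of about 0 and rejection of 4-5%. Finer recurring seasons did not help: 4.37 mmHg with quarters and 4.29 mmHg with calendar months.

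**The case against.** The strongest reply is that the faulty model is inferred. The sentence is illustrative, does not define season and does not say that the trend is dropped. If season were crossed with year, the two-per-year version would coincide with visit number and be unbiased. If season were added to the spline, the bias would also be about zero. Listing visit number separately does not fully exclude year-specific seasons, since visit windows last four to five months and a calendar season need not match a visit. The exact coding of a sensitivity analysis is also often left to a fuller document.

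This has force, and the point is conditional on the reading for that reason. It does not remove the point: season is offered as an alternative form of the one term that adjusts for time, and a person following that text would fit season in its place.

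A second reply also stands. The 3 mmHg/year is a scenario for testing power, not a forecast. Over 29.5 months it means a common drift of 3 × 29.5/12 = 7.4 mmHg, and no expected drift is given anywhere. With no drift there is no bias.

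A reader might infer that the trial's main stove estimate is compromised. The documents do not support that: the primary model keeps a spline of visit date, and neither it nor the visit-number version is biased by a linear trend.

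**Conclusion.** The point holds for one named sensitivity analysis, on the plain reading that recurring season indicators stand in for the spline. In that run the bias is about 1.5 mmHg per 1 mmHg/year of common trend. Even 0.5 mmHg/year gives 0.76 mmHg and roughly 50-58% false positives, and the stress-test trend gives 4.6 mmHg, about 2.5 times the 1.81 mmHg detectable difference. The SE of about 0.35, against 0.65-0.70 for the trend-adjusted models, makes the error look precise.

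These figures rest on the protocol's SD and correlation, a linear trend shared by both arms, visits within the Table 1 windows and two-sided alpha of 0.05. They are for systolic blood pressure only; the bias for CRP and HbA1c was not sized. It should not be inferred that drift of this size is expected, or that the authors certainly intend to drop the trend.

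**What to change.** Reword the sensitivity sentence so that season indicators enter only in addition to the spline, or to a linear trend in visit date, and never in place of it. Keep visit-number indicators as the stand-alone alternative form of f(t). If year-specific seasons were intended, the sentence should say so.

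The cost is one sentence, with no new data and no change to the primary analysis. The downside is that the season run loses its spurious precision: its detectable difference becomes about 1.96 mmHg, the same as with visit-number indicators, in place of about 0.99 mmHg (2.80 × 0.353) for season alone.
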